### Anxiety and depression

To evaluate symptoms of anxiety and depression we applied the Hospital Anxiety and Depression Scale (HADS) Portuguese validated version [22]. The HADS was originally developed by Zigmond and Snaith [23] as a screening tool to apprehend clinically significant states of anxiety and depression in a non-psychiatric hospital setting. Individual anxiety and depression scores were calculated by summation of the appropriate seven items and thus can range from 0 to 21, with higher scores indicating higher levels of anxiety or depression, respectively. In both subscales, a score between 0 and 7 is “normal,” between 8 and 10 “mild,” between 11 and 14 “moderate,” and between 15 and 21 “severe” (idem). Presence of anxiety and depression symptoms was defined when HADS scale was ≥ 11, since Snaith suggested a score ≥ 11 was indicative of “caseness” to a mood disorder [24]. This scale is used in a lot of observational studies [14, 25].

### Health characteristics

Metabolic risk is assessed by the Finnish Diabetes Risk Score-FINDRISC (FINDRISC). FINDRISC is a simple and practical tool originally designed in Finland to identify individuals at high risk of type 2 diabetes mellitus onset, without the need for laboratory tests [26, 27]. The score is based on eight easily identifiable parameters (age, body mass index, waist circumference, hypertension, physical activity level, diet, occurrence of previous hyperglycemia, and family history of diabetes) and provides a measure of the probability of developing diabetes over the next 10 years. This score is being used in different European populations [28, 29].

Participants will be asked if they had been previously diagnosed with some chronic disease (high cholesterol level, high blood pressure, heart disease, diabetes, and pulmonary disease). Self-reported abdominal circumference, height and weight and based on these data, body mass index (BMI, weight/height2, in kg/m2) will be calculated and categorized according to the World Health Organization classification in four categories: underweight (BMI < 18.5 kg/m2), normal (BMI between 18.5 and 24.9 kg/ m2), overweight (BMI between 25 and 29.9 kg/m2), and obesity (BMI ≥ 30 kg/m2) [30].

### Health related behavior

Health related behavior covers the following domains: alcohol intake (daily, occasionally, and never), consumption of fruits and vegetables, smoking habits, and physical activity.

Alcohol intake is measure by Alcohol Use Disorders Identification Test (AUDIT) developed by WHO, it is a simple and effective method of screening for unhealthy alcohol use, defined as risky or hazardous consumption or any alcohol use disorder [31].

Smoking habits (current smoker, past smoker, and never smoked) is accessed by Fagerström Test for Nicotine Dependence. This is a standard instrument for assessing the intensity of physical addiction to nicotine. The test was designed to provide an ordinal measure of nicotine dependence related to cigarette smoking. It contains six items that evaluate the quantity of cigarette consumption, the compulsion to use, and dependence [32, 33]. 

### Study validity

Data collection forms will be further monitored centrally to check for missing data or inconsistencies, including potential participant telephone contact to confirm the answers. Also, a monthly analysis of the collected data will be carried out to monitor its quality. This statistical analysis will be carried out at different levels: by teams of interviewers, by locations, age groups and gender, to minimize errors in the data.

The data collected will be stored on a specific server with a high level of security.

### Statistical analysis

Descriptive statistics will be computed to describe the baseline characteristics of the participants (gender, age, education and marital status). Normally distributed variables will be described by the mean and standard deviation. In the case of non-normal distributions, the data will be presented as median and interquartile range. For qualitative variables, absolute and relative frequencies will be calculated. At baseline comparisons between groups (e.g. with and without anxiety) will be undertaken using *t-*tests for continuous normally distributed variables or Wilcoxon for non-normally distributed variables. Chi-squared tests will be used for categorical variables, and Fisher’s Exact test will be used for categorical variables within smaller sample sizes.

Taking into consideration follow-up, the changes in HL will be evaluated by means of variance analysis with measurement repetition. After checking the statistical model pre-requisites, sociodemographic characteristics will be added by means of linear regression analysis in the final model.

For all calculations the level of statistical significance will be set to *p* < 0.05 and Stata software will be used.

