**Discussion:**

The LiSa project is a population-based study, derived from a random sampling technique that will allow the analysis of health outcomes in a representative sample of the population of the municipality of Leiria. The LiSa study will be a valuable resource for epidemiological research, as it will provide fundamental information to improve public health policies regarding health literacy in Portugal.

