### Sample size

Residents of the municipality of Leiria aged 18 years or more. A sample size of 4003 (2001 males and 2002 females) were determined. A random sample stratified by gender and age groups (18–29, 30–64, 65 or more), for a confidence level of 95% and margin of 5% error was computed, in this case the sample need to collect should be 2287 participants. However, from previous studies [14] it is known that there is a high dropout rate in longitudinal studies, reaching approximately 50% in the 3rd wave. As if pretending to make 5 waves, the sample was increased by 75%. In other words, considering a dropout rate of 75%, data from 4003 participants should be collected. See Table 1.

**Table 1 Tab1:** Sample size of LiSa cohort study

	Leiria’s population		Sample size		+ 75% dropout	
	Male	Female	Male	Female	Male	Female
18–29 years	9367	9165	380	380	665	665
30–64 years	30,295	32,625	383	383	670	670
65 ou + years	9632	12,404	380	381	665	667
**Total**	**49,294**	**54,194**	**1143**	**1144**	**2001**	**2002**

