### Recruitment phase: face-to-face interview

The team of interviewers that will carry out the baseline data collection will be composed of 32 interviewers. Prior to the start of the study, all participating interviewers will be trained, by Lisa team, to standardize procedures. This training will cover the study protocol, and topics related to coaching, study design, study characteristics, logistics, ethical and legal issues, sample selection methodology, interview procedures (exercises of roll-play) and software. Only the candidates that successfully do this training will be selected to the interviews face-to-face, to assure the quality of the data collection [15].

Interviewers must be motivated and know very well the study and its objectives. For that, an interviewer’s manual/guide was designed with all the details of the study. The interviewers are grouped in teams of four and the interviews will be done by two interviewers, a male and a female. In each team of four, there is an interviewer coordinator who will manage the interviewer teams (scheduling interviews, travel, etc.), manage conflicts that may arise and make sure that the interviewers’ interaction with the participants is carried out correctly and according to the script.

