### Data collection

At baseline a face-to-face interview will be conducted with the Computer Assisted Personal Interview (CAPI) system: all interviewers have a tablet with the software which will provide the questionnaire. The questionnaire was designed by LiSa’s research team. Both the survey and software performance were tested in a small sample of subjects, and results validated by the LiSa research team before being used by the interviewers. It is estimated it will take approximately 30 min to complete the survey.

Since there is no reliable list of households in Portugal, a random selection of points in the map of each location will be performed. Addresses will be selected, and afterwards the “random walks” will start. Interviewers will register each selected address and, if someone is at home, they will collect information on age and gender of the different people living in that address, and will give information about the study. After validation of the selected address and inhabitants, the interviews will be scheduled, or if the person is available will be immediately asked to answer the questionnaire. In order to assure the successful data collection, up to three visits to each address (one during the weekend) will be made [13]. At each address, the person whose birthday is closest to the day of the visit (aged 18 years or older) will be selected for the interview.

Between February and April 2023, five interviewers conducted a pilot study, in the largest parish in the council, with the aim of testing the proposed methodology. Taking into account that data collection went well, we will maintain this data collection methodology and start the first data collection in February 2024.

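### Table 1 plans equal age-group samples and the fieldwork is clustered, but the named analyses suit a simple random sample, so municipality-wide figures need weights and design-based variance

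*Protocol article*

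**What the plan says.** **Allocation.** The Sample size section describes "A random sample stratified by gender and age groups (18–29, 30–64, 65 or more") with each cell sized "for a confidence level of 95% and margin of 5% error was computed". Table 1 gives 380 to 383 per sex-by-age cell, or 665 to 670 after the increase for dropout.

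**Selection.** The Data collection section says that "a random selection of points in the map of each location will be performed". Random walks follow, and at each address one adult is taken by nearest birthday. The Recruitment phase section adds that "the interviews will be done by two interviewers, a male and a female".

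**Target.** The abstract and the Background aim at health literacy (HL) among the municipality's adults, and the abstract's discussion speaks of "analysis of health outcomes in a representative sample of the population of the municipality of Leiria".

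**Analysis.** The Statistical analysis section names means, medians, frequencies ("For qualitative variables, absolute and relative frequencies will be calculated"), t, Wilcoxon and Fisher's exact tests, repeated-measures analysis of variance and linear regression, and adds that "Chi-squared tests will be used for categorical variables". Weights, post-stratification, household size, clustering and design effects appear nowhere in the article.

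**The concern.** Three features of the design make this sample differ from a simple random sample of Leiria's adults: near-equal cells for age groups of very unequal size, one adult per address whatever the household size, and interviews grouped along walks. The methods named are the ordinary ones for independent, equally weighted observations.

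At stake is the main aim. An overall HL figure computed this way describes a population in which the 30–64 group has been cut from three fifths to one third and the young and old enlarged. The natural comparisons are the European and national prevalences of limited HL that the article's Discussion cites (47.6% and 61%), so errors of a few points would matter. Treating interviews from one walk as independent would also make tests and standard errors look more precise than they are.

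**Working it through.** **Inputs.** Population counts and cell sizes are from Table 1. Age-specific proportions, interviews per walk, intraclass correlations (ICCs) and household mixes are not in the article and are assumed below.

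**1. The plan's own figure.** With z = 1.96, e = 0.05 and p = 0.5 (not stated, assumed), n0 = 1.96² × 0.25 / 0.05² = 384.16. The usual finite-population correction, n0 / (1 + (n0 − 1)/N), gives 369 to 380 per cell and 2,239 in all, against the stated 2,287 (2.1% apart). The variant z²pqN / (e²(N − 1) + pq) returns the printed cells 380, 380, 383, 383, 380 and 381. Each cell was therefore sized on its own, which is why the age groups come out equal. The increase is 2,287 × 1.75 = 4,002.25, rounded up to 4,003; the six printed cells add to 4,002, which is used below.

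**2. Shares.**

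| Age | Population | Share | Planned n | Share | Sampling fraction by sex |
|---|---|---|---|---|---|
| 18–29 | 18,532 | 17.9% | 1,330 | 33.2% | 7.1–7.3% |
| 30–64 | 62,920 | 60.8% | 1,340 | 33.5% | 2.1–2.2% |
| 65+ | 22,036 | 21.3% | 1,332 | 33.3% | 5.4–6.9% |
| All | 103,488 | 100% | 4,002 | 100% | |

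Sampling fractions differ by a factor of up to 3.5.

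**3. Bias of an unweighted overall proportion.** Sample share minus population share gives

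bias = 0.153 × p(18–29) − 0.273 × p(30–64) + 0.120 × p(65+).

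The same expression holds for a mean. With assumed proportions:

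| 18–29 / 30–64 / 65+ | Unweighted | Population | Bias (points) |
|---|---|---|---|
| 40/50/60% | 50.0% | 50.3% | −0.3 |
| 50/60/80% | 63.3% | 62.5% | +0.9 |
| 5/15/50% | 23.3% | 20.7% | +2.7 |
| 45/45/75% | 55.0% | 51.4% | +3.6 |
| 20/30/10% | 20.0% | 24.0% | −3.9 |

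Biases are taken before rounding. The largest naive margin is 1.96 × √(0.25/4,002) = ±1.5 points. Young and old are both over-sampled, so a straight-line gradient nearly cancels and a curved one does not.

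**4. Precision lost to weighting.** With W the population share and f the sample share of each of the six cells, the design effect is Σ W²/f = 1.34. The effective sample size is 4,002 / 1.340 ≈ 2,986, and intervals widen by √1.34 = 1.16. Taking one adult per address adds a further factor of about 1.16 to 1.18 under assumed mixes of one to four adults.

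**5. Clustering by walk.** The design effect is 1 + (m − 1) × ICC. The article gives neither m nor the ICC. Assuming m = 5 to 20 and ICC = 0.01 to 0.05, it runs from 1 + 4 × 0.01 = 1.04 to 1 + 19 × 0.05 = 1.95. A cell of 380 sized for a 5% margin would then have a margin of about 5.1% to 7.0%.

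**The case against.** **Silence is not a statement.** The article never says that the analysis is unweighted, and a fuller analysis plan could add weights. A reader might infer a decision to ignore the design; the text does not support that. What remains is a conflict within the article: the representativeness statement does not fit Table 1 unless weights are used, and no named method supplies them.

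**The frequencies describe participants.** The sentence on frequencies belongs to a paragraph about baseline characteristics, where plain counts are normal, and the section promises p-values rather than confidence intervals. Both points stand. But the section offers no other estimator for the population-level aim.

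**The equal shares are planned, not assured.** Nearest-birthday selection is stated without age quotas, and the article does not say how equal cells will be reached. If quotas are not enforced, the age imbalance shrinks and the bias formula no longer applies at these values. Household size and clustering remain.

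**The bias may be small.** This is correct for near-linear age gradients. Estimates within a sex-by-age cell, for which the study was sized, are free of the allocation bias.

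**Interviewer effects.** A reader might divide 4,003 interviews among 16 pairs, about 250 each, and obtain design effects of 2.2 to 6.0 for ICCs of 0.005 to 0.02. The article gives 32 interviewers in teams of four but does not say that pairs are fixed. If each team had two men and two women with rotating pairs (assumed), 32 pairs of about 125 interviews would give about 1.6 to 3.5. The ICCs are assumed too, so no interviewer figure can be rested on the document.

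**Conclusion.** The point holds in conditional form. If the Table 1 cells are achieved and the Statistical analysis section is run as written, municipality-wide figures are biased by under about 1 point for near-linear age gradients. For the assumed curved patterns the bias is about 3 to 4 points, which is larger than the naive margin.

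The shares and the weighting design effect of 1.34 follow from Table 1 alone. The bias in any one outcome depends on its age pattern, which is assumed here. The loss from clustering has a known direction, but its size rests on walk size and ICC, which the article does not give.

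The stronger reading, that every result is wrong and the representativeness claim cannot be rescued, is not supported. Descriptions of participants are sound as planned, and weighting can restore the population age and sex structure without a change to the sampling.

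**What to change.** For every municipality-wide estimate and comparison, including those at follow-up, state the following in the Statistical analysis section or the analysis plan:

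- **Weights.** Use a base weight equal to the number of eligible adults at the address, post-stratified to the six population counts in Table 1. If age-sex quotas are enforced, adapt the base weight, because the number of adults is then no longer the inverse of the selection probability. Say which applies.
- **Variance.** Use design-based or cluster-robust variance, with the random-walk starting point as primary sampling unit and location as stratum. Sex-by-age cells should not be the strata: each walk cuts across them, and splitting it would discard the clustering. Use the design-based counterparts of the t and chi-squared tests, available in the Stata software already chosen.
- **Data capture.** Record starting point and interviewer in the tablet questionnaire. Ages and sexes at each address are already collected.
- **Interviewers.** Examine interviewer effects as a sensitivity analysis.
- **Wording.** Keep unweighted counts for describing participants, and make the representativeness statement conditional on weighting.

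The cost is some text and at most two recorded fields; the sampling does not change. Overall intervals become about 16% wider from the age-sex weights, with more from household weights and clustering. Age-sex weights can be built later from Table 1, but starting point and interviewer are best captured during fieldwork.

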**Methods:**

This is a prospective cohort study that collects data on HL, anxiety and depression, health characteristics, health behavior and sociodemographic data. The study population will be composed by adults (≥ 18 years old) who are non-institutionalized and living in private households in Leiria. The random sample is stratified by gender and age groups. A face-to-face interview will be conducted with the Computer Assisted Personal Interview at baseline. Follow-up will be carried out every 2 years via telephone call. The association between independent variables and health literacy is examined by means of variance analysis with measurement repetition, and taking into consideration follow-up.

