### Follow-up

The collection of new data will be carried out every 2 years via telephone call.

One of the approaches to mitigate the abandonment of participants (loss to follow-up) is to ensure good communication between the study team (interviewers, researchers, health professionals, designers, mayors) and cohort participants, using effective communication channels, updated, and provide quick feedback on health information to the participant.

The reasons why participants drop out of the study will be documented in order to analyze the bias of the study results.

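### Repeated-measures ANOVA is a poor method for HL change in a closed five-wave panel that plans for 75% loss; a mixed model on all available waves is a cheap improvement

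*Protocol article*

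**What the plan says.** All places are in the protocol article.

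- **Statistical analysis:** over follow-up, "the changes in HL will be evaluated by means of variance analysis with measurement repetition". Then, "After checking the statistical model pre-requisites", "sociodemographic characteristics will be added by means of linear regression analysis in the final model". No other longitudinal analysis of HL is given.
- **Abstract, Methods:** the same ANOVA is named for a second purpose: "The association between independent variables and health literacy is examined by means of variance analysis with measurement repetition".
- **Study design:** a closed cohort with five collection points over ten years, so people who leave are not replaced.
- **Sample size:** earlier studies show that "there is a high dropout rate in longitudinal studies, reaching approximately 50% in the 3rd wave"; for this study, "considering a dropout rate of 75%, data from 4003 participants should be collected".
- **Follow-up:** later waves are by telephone. "The reasons why participants drop out of the study will be documented in order to analyze the bias of the study results".

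**The concern.** The article fixes a method that fits badly with its own expected attrition. Classical repeated-measures ANOVA needs a score at every wave from every person analysed, so with 75% loss most of the cohort drops out of the analysis. The long-format version, with subject as a factor, keeps incomplete records. It is unbiased for change only if leaving is unrelated to a person's earlier scores.

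Measuring HL in the municipality over ten years is the main aim. If people with lower HL leave more often, completers look more literate than the population and their change over time is distorted. Recording why people leave helps to describe that problem, but the ANOVA has no step that uses the information.

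**Working it through.** **1. The plan's own figures.** 2287 × 1.75 = 4002.25, rounded up to 4003, which reproduces the stated sample. (Whether that is the right way to allow for 75% loss is a separate matter.) With 75% loss, 4003 × 0.25 = 1000.75, so about 1,000 complete records remain.

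**2. Observations used.** A constant retention per wave that leaves 25% at wave 5 is 0.25^(1/4) = 0.707. It leaves 0.707² = 50% at wave 3, which agrees with the article's other figure.
- Waves per person: 1 + 0.707 + 0.5 + 0.354 + 0.25 = 2.81.
- Observations collected: 4003 × 2.81 ≈ 11,250.
- Used by a complete-record ANOVA: 1,001 × 5 = 5,005.
- Discarded: 1 - 5,005/11,250 ≈ 55%.

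This holds whatever the reasons for dropout.

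**3. Assumptions for bias and precision.** The article gives no SD, within-person correlation or dropout mechanism. Assumed: HL index SD 8, equal correlation 0.5 between waves, true change zero, 70.7% retention per wave and no return after dropout. Simulations had 4,003 people, five waves and 200 replicates per setting.

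**4. Precision.** The SD of a within-person difference is 8 × √(2 × (1 - 0.5)) = 8. The standard error of the wave 1 to wave 3 change among completers is therefore 8/√1001 ≈ 0.25, against about 0.16 for the mixed model in simulation. The gain is smaller for wave 1 to wave 5, because nobody who left has a wave-5 score.

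**5. Dropout unrelated to HL (MCAR).** Bias in change is about zero for every method.

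**6. Dropout depending on the last observed HL (MAR).** Bias in HL points for wave 5 minus wave 1, and for completers' wave-5 level. Repeat runs agree to about 0.1.

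| Continuation odds ratio per SD | Completers, change | Subject-factor ANOVA, change | Mixed model, change | Completers, wave-5 level |
|---|---|---|---|---|
| 1.2 | -0.2 | -0.45 | about 0 | +0.9 |
| 1.5 | -0.4 | -0.9 | about 0 | +1.8 |
| 2.0 | -0.7 | -1.5 | about 0 | +2.8 |

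A second set of simulations used equal correlation 0.6 or autoregressive correlation 0.7, with log-odds of staying of 0.25 to 1.0 per SD. Completer change bias was -0.3 to -1.1 when the previous wave drove dropout and -1.0 to -5.1 when baseline HL did. The likelihood-based model stayed within -0.06 to +0.05 throughout.

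**7. Dropout depending on current, unobserved HL (MNAR), with the assumptions of step 3.**
- Odds ratio 1.5: change bias is about +0.4 for completers and +1.0 for the mixed model. For the wave-5 level the order reverses: +2.2 against +1.0.
- Odds ratio 2.0: change bias is +0.7 and +1.7.

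**The case against.** **Bias is not shown.** Nothing in the article says that people with low HL leave more often. This stands: a reader might infer that the planned ANOVA will bias the results, but the documents support only that it can. Without such dropout, the cost is precision.

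**The mixed model is favoured by the set-up.** Step 6 uses the mechanism under which a likelihood method is unbiased by design. This also stands, and step 7 shows the other side. It is a reason to add an MNAR sensitivity analysis. It does not rescue the ANOVA, which loses information under MCAR and is biased under MAR.

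**The biases in change are small.** At odds ratio 1.5 they are 0.4/8 = 0.05 SD and 0.9/8 = 0.11 SD, against middle HL categories 8 to 9 points wide. The larger bias is in level, while the Statistical analysis section assigns the ANOVA to change. Both remarks are fair, though level over time is part of the stated aim.

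**The regression step.** A reader might infer that covariates go into an ordinary regression on pooled person-waves, with standard errors that are too small. On that reading, with correlation 0.5 and unequal rows per person, the design effect would be about 2.34 and a nominal 5% test of a person-level covariate would reject about 20% of the time. The article does not say this. Its sentence could equally mean adding covariates to the repeated-measures model, or regressing one change score per person, and it promises a check of model requirements. No error in the standard errors is therefore established. The point is only that one joint model would settle the matter.

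**An unseen analysis plan may cover missing data.** It may, and its absence here is no finding. The point concerns the method that the article does name. The article does not call this analysis primary, but gives no other longitudinal analysis for its main aim.

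**Conclusion.** The point holds in a limited form. The named ANOVA is ill-suited to a closed panel that expects to keep a quarter of its members. The firm part is the loss of information: in complete-record form, about 1,000 of 4,003 people and about 45% of the observations are used. This rests on the article's own dropout figures and, for the observation count, on even attrition between waves.

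The bias is conditional. It is absent under MCAR. Under MAR it ranges from -0.2 to -0.7 points (completers) or -0.45 to -1.5 (subject-factor ANOVA) for change, and from +0.9 to +2.8 for completers' wave-5 level. These sizes are illustrative because SD, correlation and dropout strength are assumed; other plausible choices gave larger values. The mixed model is better under MCAR and MAR, but not uniformly better under MNAR.

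This is a cheap improvement that should be made. It is not a fatal flaw, since data collection is unaffected.

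**What to change.** In the Statistical analysis section, and to match in the abstract:

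1. Replace the repeated-measures ANOVA with a likelihood-based linear mixed model (Stata `mixed`) that uses every available wave of every participant, with wave as a categorical factor and an unstructured or random-intercept covariance.
2. Enter the sex-by-age strata and the sociodemographic variables, with their interactions with wave, in that same model. Drop the separate linear regression step, so that within-person correlation is accounted for.
3. State that this model relies on dropout being MAR. Add a sensitivity analysis for MNAR dropout, such as delta-adjusted or pattern-mixture estimates. Retention weighting can accompany it but cannot replace it, since it also assumes MAR.

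The cost is one paragraph of text and slightly more modelling, with the same data and software. The article puts baseline collection from February 2024 and follow-up every two years, so the method can be fixed before follow-up data exist.
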